## Abstract

**Background:**

Multimorbidity, defined as two or more concurrent chronic diseases within the same individual, is becoming the clinical norm within primary care. Given the burden of multimorbidity on individuals, carers and health care systems, there is a need for effective self-management programmes. Promoting active participation within their clinical care and following a healthy lifestyle will help empower patients and target lifestyle factors that are exacerbating their conditions. The aim of this study is to establish whether a tailored, structured self-management programme can improve levels of physical activity at 12 months, in people with multimorbidity.

**Methods/design:**

This study is a single-centre randomised controlled trial, with follow-up at 6 and 12 months. The primary outcome is change in objectively assessed average daily physical activity at 12 months. Secondary outcomes include medication adherence, lifestyle behaviours, quality of life, chronic disease self-efficacy and self-efficacy for exercise. Anthropometric and clinical measurements include blood pressure, muscle strength, lipid profile, kidney function and glycated haemoglobin (HbA1c). Participants are recruited from primary care. Those between 40 and 85 years of age with multimorbidity, with a good understanding of written and verbal English, who are able to give informed consent, have access to a mobile phone for use in study activities and are able to walk independently will be invited to participate. Multimorbidity is defined as two or more of the chronic conditions listed in the Quality and Outcomes Framework. A total of 338 participants will be randomly assigned, with stratification for gender and ethnicity, to either the control group, receiving usual care, or the intervention group, who are invited to the Movement through Active Personalised engagement programme. This involves attending four group-based self-management sessions aimed at increasing physical activity, mastering emotions, managing treatments and using effective communication. The sessions are delivered by trained facilitators, and regular text messages during the study period provide ongoing support. Changes in primary and secondary outcomes will be assessed, and an economic evaluation of the intervention undertaken.

**Discussion:**

This study will provide new evidence on whether physical activity can be promoted alongside other self-management strategies in a multimorbid population and whether this leads to improvements in clinical, biomedical, psychological and quality of life outcomes.

**Trial registration:**

ISRCTN, ISRCTN 42791781. Registered on 14 March 2017.

**Electronic supplementary material:**

The online version of this article (10.1186/s13063-018-2939-2) contains supplementary material, which is available to authorized users.

## Background

Multimorbidity, defined by the World Health Organization as two or more concurrent chronic health conditions within the same individual [1], is becoming the clinical norm within the ageing population in primary care [2]. In developed countries the prevalence of multimorbidity in the general population is estimated to be between 25 to 55% at 60 years of age and as high as 80% in those older than 75 years [3, 4]. Patients with multimorbidity are more likely to die prematurely, be admitted to hospital and have longer hospital stays than those with single conditions [5, 6]. Multimorbidity leads to a decline in functional status and quality of life, and patients are more likely to experience depression and to be receiving multiple drugs with consequent difficulties with adherence [7, 8]. Multimorbidity increases health care expenditure compared to that for patients with a single chronic disease and requires bespoke systems of management [9]. However, despite this new clinical reality, routine health care systems are still largely based around single disease management pathways and guidelines, which can result in overtreatment or sub-optimal treatment and fragmented care. These problems are exacerbated in those who are elderly [10], from areas of high social deprivation [11] or from black and minority ethnic backgrounds [12].

An effective self-management and healthy lifestyle programme helps in empowering patients and facilitating active participation within their clinical care and targeting lifestyle factors that are exacerbating their conditions. Self-management programmes are an integral part of many disease management pathways and have been recommended in the UK by the National Institute for Health and Care Excellence (NICE) [13–17]. However, self-management and lifestyle interventions have not been specifically tailored or implemented for use in those with multimorbidity and are not mentioned in the NICE Guidelines for the Management of Multimorbid Conditions [9].

Physical inactivity is associated with an increased risk of all-cause mortality, cardiometabolic disease, musculoskeletal problems, declining cognitive function, poor psychological health and reduced quality of life [18]. Therefore, given these wide-ranging links across the chronic disease spectrum, it is unsurprising that physical activity has also been associated with multimorbidity [19–21]. It has been shown that an increase in ambulatory activity of 2000 steps/day is associated with an 8% reduction in the relative risk of cardiovascular mortality or morbidity in those with prediabetes and existing cardiovascular disease [22]. Others have shown that physical activity-based interventions have a similar level of efficacy compared to established pharmaceutical therapies in the secondary prevention of cardiovascular disease, whilst also effectively reducing symptoms of depression in those with chronic disease, improving measures of functional ability and improving cognitive function [23–25]. Improvements in physical functioning following physical activity interventions have been observed in multimorbidity [26]. However, few trials have looked at the effectiveness of interventions designed to improve lifestyle outcomes in patients with multimorbidity in primary care [27], and the evidence related to changes in lifestyle behaviours such as diet and physical activity is conflicting [28–30]. This observational and interventional evidence, across multiple outcomes and conditions, suggests that physical activity can be conceptualised as a composite marker of overall health status. A positive change in physical activity would therefore ensure an intervention targets many of the clinical factors associated with multimorbidity. The present study aims to develop and evaluate a self-management programme for patients with multimorbidity that focusses on lifestyle factors such as physical activity, medication adherence and self-management and can be translated into primary care.

## Methods/design

### Aims and objectives

The aims of this trial are to:Test the effectiveness of a structured self-management programme on increasing the levels of physical activity using accelerometry at 12 months in people with multimorbidityAssess the effectiveness of the programme on improving clinical measures including blood pressure, lipid profile, body weight and grip strengthAssess the effectiveness of the programme on improving self-management outcomes including medication adherence, lifestyle behaviours, clinical outcomes, quality of life and self-efficacyCarry out an economic evaluation of the intervention. This will assess implementation and running costs, as well as short-term and long-term cost-effectiveness

### Study design

The study is a single-site, two-arm, parallel, 12-month randomised controlled trial (RCT) testing the effectiveness of a tailored structured self-management programme. Participants are recruited from primary care in Leicestershire, UK. For the purposes of the trial, multimorbidity is defined using the most common definition, i.e. two or more long-term conditions [11, 31]. Figure 1 describes the study flow and participant progression through the study. The study is sponsored by the University of Leicester, and ethical approval was granted by West Midlands – South Birmingham Research Ethics Committee and the Health Research Authority. The study was prospectively registered (ISRCTN 42791781), and the completed Standard Protocol Items: Recommendations for Interventional Trials (SPIRIT) checklist is available as an additional document (Additional file 1).

**Fig. 1 Fig1:**
[figure not shown]
Schematic representation of study

### Recruitment and informed consent

Potential participants with multimorbidity (see the next section for the definition) are identified by a bespoke electronic Morbidity Information Query and Export Syntax (MIQUEST) search [32] of the practice’s electronic health records, and the list of potential participants is reviewed by an appropriate member of the practice staff. Potential participants are then sent a recruitment pack containing an invitation letter, a brief information leaflet detailing the study and a reply slip. Reply slips from those interested in taking part are returned to the study team. A member of the study team then contacts the patient by telephone to screen them and arrange a baseline visit to formally confirm eligibility, undertake informed consent and collect the baseline data. Following the telephone screening, the patient is sent the full Participant Information Leaflet (PIL) and a letter confirming the details of the baseline clinic. These documents are sent at least 5 days before the appointment to ensure that patients have a minimum of 24 h to read the PIL and ask questions of the study team prior to giving consent. Recruitment clinics are staffed by trained research nurses and health care assistants employed by the University Hospitals of Leicester National Health Service (NHS) Trust, and the clinics are held in local community venues. After confirming the patient’s eligibility, written informed consent is taken by a member of the team trained in the procedure.

### Inclusion and exclusion criteria

For the purpose of the study, multimorbidity is defined as having two or more of the chronic conditions included in the Quality and Outcomes Framework (QOF) [33] with the exception of those classified under palliative care or within the mental health and neurology category, other than depression (Table 1). These conditions are excluded given their complexity and specialist needs, which are likely to be beyond general group-based self-management interventions. ’Primary prevention of cardiovascular disease’ is not included as a chronic condition, as patients under this category would already have a diagnosis of hypertension and/or type 2 diabetes. Obesity is not considered as a separate condition, since it is ubiquitous in many chronic diseases [34]. Patients undergoing treatment for cancer are excluded, but if in remission they can take part if they have two other chronic conditions. Patients with both asthma and chronic obstructive pulmonary disease are included only if they have another morbidity. There are no limitations concerning disease duration, medication use and/or initiation of new treatment unless there are specific recommendations for bed rest and minimising physical activity for a specific condition.

**Table 1 Tab1:** Conditions included in the Quality and Outcomes Framework (QOF) [33]

Cardiovascular	Secondary prevention of coronary heart disease
	Cardiovascular disease, primary prevention*
	Peripheral arterial disease
	Atrial fibrillation disease
	Heart failure
	Hypertension
	Stroke/transient ischaemic attack
Respiratory	Asthma**
	Chronic obstructive pulmonary disease**
Lifestyle	Obesity*
High dependency and long-term conditions	Cancer***
	Chronic kidney disease
	Diabetes mellitus
	Hypothyroidism
	Palliative care****
Mental health and neurology	Depression
	Dementia****
	Learning disability****
	Mental health****
	Epilepsy****
Musculoskeletal	Osteoporosis
	Rheumatoid arthritis

***Patients with these conditions require at least two other conditions in order to be included

**Patients with both asthma and chronic obstructive pulmonary disease require at least one other condition to be included

*****Patients undergoing cancer treatment are excluded. If treatment is finished they can participate, but two other conditions are required to be included

******Patients with these conditions are excluded

In addition, patients must be aged between 40 to 85 years of age inclusive, have a good understanding of written and verbal English, be able to give informed consent, have access to a mobile phone for use in study activities, be willing and able to attend the recruitment clinics and self-management sessions and be able to walk independently. Patients who have limited understanding of written and verbal English, are pregnant or are currently participating or have participated in another interventional trial in the previous 12 weeks are excluded. Patients with frailty (defined as one or more of the following: living in care homes or institutions; needing daily support for activities such as washing, cooking and household tasks; having had unintentional significant weight loss in the last 3 to 6 months; having a body mass index of less than 18.5 kg/m^2^) are also excluded from the study.

### Randomisation and blinding

Study identification numbers are assigned sequentially, and participants are individually randomised (1:1) stratified by gender (men; women) and ethnicity (White European; other) using a variable block size after their baseline assessment. In order to prevent contamination, an exception is made for individuals from the same household who are allocated to the same group. The randomisation schedule was developed by an independent statistician, and allocation of randomisation is carried out by a researcher independent of the team. Randomisation dictates whether the participant receives standard care or is invited to attend the Movement through Active Personalised engagement (MAP) programme.

After randomisation both groups are sent a letter informing them of the outcome of the randomisation; in addition, intervention participants are contacted by telephone to discuss the dates available for them to attend the intervention. They are then sent a letter confirming the venue, dates and times of the programme. Since the intervention is a group self-management programme, participants and the central study team cannot be blinded to the randomisation. The research nurses who run the follow-up clinics are not informed of the randomisation of the participants attending, and staff analysing accelerometer data to derive the primary outcome are blinded.

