### Statistical analysis

A Consolidated Standards of Reporting Trials (CONSORT) diagram will summarise the flow of participants through the study. Descriptive characteristics at baseline will be summarised by arm. Numbers (with percentages) for binary and categorical variables, and means (and standard deviations) or medians (with lower and upper quartiles) as appropriate for continuous variables will be presented. Preliminary graphical and tabular presentations of the data will be inspected for the correct statistical modelling assumptions.

The primary analyses will use a complete case population (i.e. participants with a complete log and valid outcome measurements). For the primary outcome (change in average daily physical activity), the intervention group will be compared to the control using a linear regression model with a binary indicator for randomisation group as the explanatory variable; terms for the stratification factors (ethnicity and gender) as confounders; and adjustment for the change from baseline in accelerometer wear time and baseline average daily physical activity. Sensitivity analyses will include a per-protocol analysis and an intention-to-treat analysis where missing data will be imputed using multiple imputation or another suitable method. Sensitivity analysis will also test whether outcomes are robust if physical activity data are restricted to those with at least 3 days of valid data. Interaction effects will be fitted between intervention arm and gender (male vs. female), and ethnicity (White European vs. other). If the interaction term is statistically significant (at the 10% level), then stratified analyses will be performed for that factor using the same model as the primary analyses. Secondary outcomes will be analysed using similar methods as in the main analysis, with an appropriate model selected dependent on the distribution of the outcome. A detailed statistical analysis plan will be written and approved before the database is locked.

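### Household members are allocated together, but the primary regression has no household term, and the article does not rule out a later member joining with a known arm

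*Protocol article*

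**What the plan says.** The general rule, under Randomisation and blinding in the Protocol article, is that "participants are individually randomised (1:1) stratified by gender (men; women) and ethnicity (White European; other) using a variable block size after their baseline assessment". The next sentence gives an exemption, justified as protection against contamination: "an exception is made for individuals from the same household who are allocated to the same group". The schedule comes from an independent statistician, and a researcher outside the team carries out the allocation.

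The same section makes the result known: "After randomisation both groups are sent a letter informing them of the outcome of the randomisation". It adds that "participants and the central study team cannot be blinded to the randomisation". Under Recruitment and informed consent, "A member of the study team then contacts the patient by telephone to screen them and arrange a baseline visit to formally confirm eligibility". The article does not say whether members of one household must be enrolled or allocated at the same time.

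Under Statistical analysis, the primary outcome is compared by a "linear regression model with a binary indicator for randomisation group as the explanatory variable", with "terms for the stratification factors (ethnicity and gender) as confounders", plus baseline activity and change in wear time. Household does not appear. Secondary outcomes are to be handled in a similar way. The Sample size section gives 202 evaluable and 338 recruited participants and mentions no design effect.

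**The concern.** Two separate consequences follow from the household exemption.

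**Precision.** Two people in one household share an arm by design. They probably also share habits, meals and outings, so their changes in activity may be positively correlated. The reason given for the exemption, contamination between members, itself implies that they influence each other. An ordinary regression counts such a pair as two independent observations. With positive residual correlation the standard error is then too small, the confidence interval too narrow, and the test rejects more often than 5% under the null.

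**Concealment.** If one member is randomised and told the result before another enters, no new draw is made for the second. The arm is already determined, and the first member and the unblinded central team know it. The independent schedule and independent allocator do not protect concealment in that case. The second person could join, or decline, because of the arm.

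**Working it through.** **1. The plan's own figure.** Inputs from Sample size: difference 2.1 m*g*, SD 5.3 m*g*, power 80%, significance level 5% (taken as two-sided).
- Normal approximation: n per arm = 2 × (1.960 + 0.842)² × 5.3² / 2.1² ≈ 100.0.
- Two-sample t-test: 100.96, so 101 per arm, or 202. This matches.
- Recruitment: 101 / (1 − 0.20 − 0.20) = 168.3, so 169 per arm, or 338. This matches.

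Both figures reproduce exactly with independent observations and no clustering allowance.

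**2. Variance with same-arm pairs.** Let p be the share of participants in household pairs and r the correlation within a pair that remains after adjustment for baseline activity, gender, ethnicity and change in wear time. An arm of n people contains pn/2 pairs, and each pair adds 2rσ² to the variance of the arm total:

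Var(total) = nσ² + (pn/2)(2rσ²) = nσ²(1 + pr).

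The true variance of the treatment difference is therefore 1 + pr times the one that the model reports.

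**3. Type I error.** Actual size = 2 × [1 − Φ(1.96 / √(1 + pr))]. The article gives neither p nor r; the values below are assumptions.

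| p | r | 1 + pr | √(1 + pr) | True type I error |
|---|---|---|---|---|
| 10% | 0.2 | 1.02 | 1.010 | 5.2% |
| 10% | 0.5 | 1.05 | 1.025 | 5.6% |
| 20% | 0.2 | 1.04 | 1.020 | 5.5% |
| 20% | 0.5 | 1.10 | 1.049 | 6.2% |

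The reported standard error is about 1% too small at the lower corner (1/1.010 = 0.990) and about 5% too small at the upper (1/1.049 = 0.953). A simulation with 202 participants and 8,000 repetitions per setting (standard error about 0.25 percentage points) gave 5.7% at p = 10%, r = 0.5 and 6.0% at p = 20%, r = 0.5. The formula gives 5.6% and 6.2%.

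**4. Power under a correct analysis.** With 101 per arm, the effective number per arm is 101/(1 + pr). By the normal approximation, power goes from 80.4% with no clustering to 76.6% at p = 20%, r = 0.5.

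**5. Concealment.** No arithmetic applies. Three statements have to be read together: members share an arm, each participant is told the result after randomisation, and the team that screens and books visits is not stated to be unaware of earlier allocations. If entry is simultaneous there is no gap. If entry is staggered, the later member's arm is fixed before consent. The article does not say which applies.

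**The case against.** The strongest reply is that the choice of standard error for a few co-resident pairs belongs in the statistical analysis plan, which the article promises before database lock and which is not shown. Clustered errors could be added without contradicting any sentence of the article. That is fair, and it keeps the point modest. It does not remove it: the article sets out the primary model and its covariates in detail, states the household rule, and does not connect the two. An analysis plan could repair the standard errors, but it could not restore concealment for someone who joined knowing the arm.

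It is also right that p and r are assumed, and that adjustment for baseline activity may leave r lower than a raw household correlation. The effect could be close to nil.

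Four stronger readings are tempting, and the documents do not support them.
- *The article contradicts itself on the unit of randomisation.* It does not. The exemption is openly declared, with its reason.
- *Concealment has been broken.* Nothing says that household members entered at different times, or how often. A condensed article may also omit a rule that the full protocol contains.
- *Copying an allocation to a partner of the other gender upsets the blocks in that stratum.* The article does not say whether a slot on the schedule is used, skipped or overridden, so this would be a guess. The model adjusts for both stratification factors in any case.
- *The sample size is wrong.* It is calculated correctly for independent participants.

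**Conclusion.** The point holds in a limited form. For participants who share a household, the allocated unit is the household, and the primary model as written does not reflect that. If residual within-household correlation is positive, standard errors are slightly too small: variance inflation of 2 to 10% and a true type I error of about 5.2 to 6.2%, for assumed p = 10 to 20% and r = 0.2 to 0.5. This would not change the reading of a clear result, but it could matter for a borderline one.

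The concealment question is conditional on staggered entry. It is an unclear procedure, not a demonstrated bias, and it touches only later-joining members. The household exemption itself is a reasonable safeguard against contamination and is not in dispute.

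**What to change.** - Record a household identifier for every participant, including those already enrolled.
- In the primary and secondary models, use household-clustered standard errors or a household random effect. The covariates stay as they are.
- Add a sensitivity analysis that keeps only the first-enrolled member of each household. It removes the within-household correlation and also addresses later members who may have joined with a known arm. If all sharing is in pairs, it drops p/2 of participants: about 10 to 20 of 202 for p = 10 to 20%.
- Where members of a household are still to be recruited, allocate them together, once, after all have consented and completed baseline.

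The analysis changes cost one identifier and slightly wider intervals (about 1 to 5% over the assumed range). The last step is procedural. Recruitment is under way, and Protocol version shows that an earlier change to the randomisation procedure went through as a substantial amendment, so this step may need one unless the full protocol already provides for it. Participants already allocated cannot be re-randomised; for them the first three steps apply.
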